### **7.5 SUPERIORITY ANALYSIS**

If there is clearly insufficient evidence to conclude futility, there is potential for analysis of the primary outcome to assess superiority (see Appendix C for correspondence).

Recall the null hypothesis for the futility design from section 4.2:

$$H_0: \mu_s - \mu_p \leq -3.$$

This is the *pre-specified superiority*. Now consider the null hypothesis of a superiority design (i.e. *zero treatment effect*),

$$H_0^{(s)}: \mu_s - \mu_p = 0.$$

These two parameter subspaces are mutually exclusive, such that if one null hypothesis is true the other must be false. Therefore, at most only one type I error can ever be committed, whatever the nature of the true state may be. We conclude there is no need to adjust for type I error rate inflation, and there are no multiple testing issues associated with a further superiority analysis. A visual example of potential confidence intervals, for both futility and superiority analyses, are presented in Figure 3.

### Possible Scenarios for Observed Differences Between Groups for Futility and Superiority Hypotheses

[figure not shown]

Figure 3: Possible scenarios for observed group differences in the change of MDS-UPDRS between baseline and 24 months under the assumptions of a futility and superiority analysis. The black circles are the difference between group means (point estimate). The red lines are two-sided 80% confidence intervals if the study is futile (i.e.  $p < 0.1$ ) and blue lines are two-sided 80% confidence interval if the study is non-futile (i.e.  $p \geq 0.1$ ). The green lines are the 95% confidence interval estimated with the same data under the assumptions for a superiority analysis. The dashed grey line at the MCID is the minimal clinically important difference. The dotted grey line at CV is the critical value from student's t-distribution; the point estimate should be above value (to the right of this line) to demonstrate futility.

## 8 ANALYSIS OF SECONDARY OUTCOMES

### 8.1 SECONDARY OUTCOME VARIABLES

Where available, the secondary outcomes will be analysed:

- (i) at 24 months;
- (ii) using repeated measures modelling to include data at baseline, 12 and 24 months.

A list of the secondary outcomes, whether the patient was measured in the ON or OFF state and the objective of the measures are presented in Table 3.

| Outcome                                                     | State | Objective                                                                             |
|-------------------------------------------------------------|-------|---------------------------------------------------------------------------------------|
| MDS-UPDRS part II                                           | ON    | Impact on motor experiences of daily living                                           |
| MDS-UPDRS Total                                             | ON    | Impact on burden and extent of PD                                                     |
| Brain tap test
(number of key presses in 30 seconds)     | OFF   | Impact on timed motor test                                                            |
| 10MWT
(successfully completed and mean time to complete) | OFF   | Impact on timed motor test and distinguish symptomatic from disease modifying effects |
| MADRS Total score                                           | ON    | Impact on mood                                                                        |
| ACE-III Total score                                         | ON    | Impact on cognitive abilities                                                         |
| NMSS Total score                                            | ON    | Impact on non-motor symptoms                                                          |
| KPPS Total score                                            | ON    | Impact on non-motor symptoms                                                          |
| PDQ-39 Total score                                          | ON    | Impact on activities of daily living                                                  |
| Total cholesterol level                                     |       | Safety of Simvastatin                                                                 |
| HDL cholesterol level                                       |       | Safety of Simvastatin                                                                 |
| Total/HDL cholesterol ratio                                 |       | Safety of Simvastatin                                                                 |
| Incidents of diabetes at 24 months                          |       | Safety of Simvastatin                                                                 |
| LED                                                         |       | Distinguish symptomatic from disease modifying effects                                |
| Number of capsules every 6 months                           |       | Tolerability of simvastatin and trial protocol                                        |

Table 3: Secondary Outcomes and the objectives they will be used to assess.

## 8.2 SECONDARY OUTCOMES ANALYSIS

Continuous secondary outcome measures will be analysed:

- (i) at 24 months using mixed effects, linear regression models;
- (ii) across baseline, 12 and 24 months using repeated measures linear models.

Since incidence of diabetes is a binary measure only observed at 24 months, this secondary outcome will be modelled using a mixed effects logistic regression model.

The models will be adjusted by the covariates described in section 6.2, with the exception of the repeated measures models, which will not include the baseline measure as a covariate (as baseline data are included in the outcome being modelled).

As not all participants will be able to complete the 10MWT, the ability to complete the test, as well as the time, are both valuable indicators of PD progression. Therefore, we will analyse time and successful completion of the 10MWT as two components of this outcome measure.

We will model completing the 10MWT as:

- binary data – whether participant successfully completed at least one 10MWT (yes or no);
- continuous data - mean time, of participants who are able to complete at least one 10MWT.

The number of capsules and percentage of expected capsules returned every month will be reported for both of the allocated groups.

The secondary outcomes will not be tested under a futility hypothesis framework: allocated group differences will be assessed at the two-sided 5% level of significance and reported with two-sided 95% confidence intervals. As the trial is not powered to detect clinically meaningful differences on the secondary outcome measures, and no adjustments for multiplicity will be made, the results of the analyses of secondary outcomes will be interpreted and reported as exploratory only.

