  - ix. *Cholesterol levels* – this will include measurements of total, HDL, total/HDL ratio cholesterol levels.
  - x. *King's PD pain scale (KPPS)* total score - a PD specific pain score consisting of 14 items within seven domains: musculoskeletal pain (1 item), chronic pain (2 items), fluctuation related pain (3 items), nocturnal pain (2 items), orofacial pain (3 items), discoloration and Oedema/swelling (2 items) and radicular pain (1 item). Each item is scored for severity (0-3) and frequency (0-4).
  - xi. *EuroQoL 5D-5L health status questionnaire (EQ-5D-5L)*.

At 24 months incidence of diabetes mellitus, determined by a glycated haemoglobin (HbA1c) level  $\geq 6.5\%$  (48mmol/mol) (WHO 2011), will also be recorded.

Every two months the safety and tolerability data will be gathered, using adverse events reporting, via telephone contacts (2 weeks, 2, 4, 8, 10, 14, 16, 20 and 22 months post-baseline) or during a follow-up visit (baseline and at 1, 6, 12, 24 and 26 months post-baseline). In addition, the number of capsules returned will be recorded every 6 months, in order to aid the determination of tolerability and compliance.

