### **3.4.2 Exclusion Criteria**

Potential participants meeting any of the following criteria will be excluded from study participation:

- Diagnosis, or suspicion, of other cause for parkinsonism
- Known abnormality on CT or MRI brain imaging considered to be causing symptoms or signs of neurological dysfunction, or considered likely to compromise compliance with study protocol
- Concurrent dementia defined by MoCA score  $< 21$
- Concurrent severe depression defined by MADRS score  $> 31$
- Prior intracerebral surgical intervention for PD including deep brain stimulation, lesional surgery, growth factor administration, gene therapy or cell transplantation
- Already actively participating in a research study that might conflict with this trial
- Prior or current use of statins as a lipid lowering therapy
- Intolerance to statins
- Untreated hypothyroidism

- End stage renal disease (creatinine clearance < 30 mL/min) or history of severe cardiac disease (angina, myocardial infarction or cardiac surgery in preceding two years)
- Estimated Glomerular Filtration rate (eGFR) < 30 mL/min
- History of alcoholism or liver impairment
- Creatine kinase (CK) > 1.1 x upper limit of normal (ULN)
- Aspartate transaminase (AST) or alanine transaminase (ALT) > 1.1 x ULN
- Females who are pregnant or breast feeding or of child-bearing potential and unwilling to use appropriate contraception methods whilst on trial treatment
- Currently taking any medication contraindicated with Simvastatin use (Appendix 2 of the protocol v4.5)
- Any requirement for statin use
- Regular participation in endurance or high-impact sports
- Unable to abstain from consumption of grapefruit-based products

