## 5.2 BASELINE CHARACTERISTICS AND DEMOGRAPHICS

The demographic data will include:

- Age in years at baseline
- Gender
- Body Mass Index (BMI)
- Ethnic origin
- Smoking status
- Modified Hoehn & Yahr score
- Age in years of PD onset
- Number of years since PD diagnosis at baseline
- Diabetes status at screening
- QRISK® 2 score
- Montreal Cognitive Assessment Score (MoCA)
- Aspartate transaminase (AST)
- Alanine transaminase (ALT)
- Creatine kinase (CK)

The data will be summarised using descriptive statistics for all recruited participants. Summaries will be produced for participant's who only participate in the 1-month low dose phase of the study.

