### 6.2 ADJUSTMENTS

The primary analysis of the primary and secondary outcomes will include fixed effects adjustments baseline outcome, gender, age at baseline and modified Hoehn and Yahr score. Recruiting site will be included as a random effect in order to account for any potential unknown variation associated with each site.

In addition to the adjustments specified in the protocol, we will also include duration of PD, as recent evidence suggests that the rate of change in MDS-UPDRS differs according to disease duration. If there is a suggestion from a visual inspection of any large difference in any of the other baseline characteristics/ demographics between allocated groups, sensitivity analysis will include additional adjustments for such a covariate.

For completeness and in line with EMA guidance, the results of models only including adjustment for baseline scores (where available) will also be presented.

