EMS - electromagnetic sensor; MADRS - Montgomery and Asberg Depression Rating Scale; ACE-III - The Addenbrooke's Cognitive Assessment-III (ACE-III); NMSS - Non-Motor Symptom assessment scale (NMSS); PDQ-39 - Parkinson's disease Questionnaire (PDQ-39); LED - levodopa-equivalent dose; KPPS - King's PD pain scale; EQ-5D-5L - EuroQoL 5D-5L health status questionnaire.

\* Differences are adjusted for outcome measure at baseline (where available), recruiting site and modified Hoehn & Yahr score, disease duration, gender and age at baseline.

Table 9: Differences between placebo and intervention group (i.e. placebo – intervention) with corresponding 95% confidence intervals for all secondary outcomes.

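### The diabetes incidence outcome is scored from 24-month HbA1c alone with no at-risk population, so as written it measures prevalence and pulls the odds ratio towards 1

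*SAP*

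**What the plan says.** - **Definition.** SAP 2.2.1: "At 24 months incidence of diabetes mellitus, determined by a glycated haemoglobin (HbA1c) level" of at least 6.5% (48 mmol/mol). Table 1 in section 4.5 marks diabetes at 24 months and at no other visit.
- **Purpose.** Table 3 in section 8.1 lists "Incidents of diabetes at 24 months" under the safety of simvastatin.
- **Model.** Section 8.2 gives the reason for its choice of model as "Since incidence of diabetes is a binary measure only observed at 24 months", and says that "this secondary outcome will be modelled using a mixed effects logistic regression model". It names no analysis population for this outcome.
- **Covariates.** Section 6.2 says that the analyses "will include fixed effects adjustments baseline outcome, gender, age at baseline and modified Hoehn and Yahr score"; it then adds disease duration, with site as a random effect. The footnote to Table 9 limits the first of these terms: "Differences are adjusted for outcome measure at baseline (where available". Table 1 gives diabetes no baseline measure.
- **Entry.** The exclusions in 3.4.2 do not include diabetes. The nearest is "Any requirement for statin use".
- **Screening status.** Section 5.2 lists "Diabetes status at screening" as a baseline descriptor, and Table 7 tabulates it as none, type 1 or type 2.

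**The concern.** An incidence needs a group free of the condition at the start. The SAP names the outcome as incidence, but its only scoring rule is a single threshold at one visit. Nothing stops people with diabetes from entering, and Table 7 reserves rows for them. The variable that would identify them is collected and then not used in the analysis.

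Two kinds of participant are affected. Someone diabetic at entry whose 24-month HbA1c is at or above the threshold is scored as an event. Someone diabetic at entry but below the threshold is scored as a non-event and stays in the denominator, although a new onset was never possible. The first kind adds a similar background to both arms and attenuates the odds ratio, which is the measure a logistic model reports.

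At stake is the SAP's only dedicated diabetes analysis. Section 9 does not replace it: diabetes is not on its list of known statin effects, and adverse events are summarised by organ system only when more than 5% of the safety population report one.

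**Working it through.** **The plan's own figures.** The SAP gives no event rate, prevalence or power for diabetes. Its sample size (57, 79, then 99 per group) concerns the primary outcome. It reproduces: 57 per group for a 3-point margin, SD 7.5, one-sided 10% and 80% power; 57/0.85² = 78.9, so 79; 79/0.80 = 98.75, so 99. It serves here only to give about 79 per arm at 24 months (99 × 0.80 = 79.2). Section 4.10.3 says 24-month blood results will be missing for the COVID-19 population, so the true number is lower.

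**Assumed inputs (none are in the SAP).**
- *p*: share diabetic at entry, 2%, 5% or 10%, equal in both arms.
- *s*: share of those at or above the threshold at 24 months, 100% or 70%, equal in both arms.
- *r*: new-case risk among those not diabetic at entry; three pairs, placebo v simvastatin.

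**Formula.** Observed risk in an arm: q = p·s + (1 − p)·r. Odds ratio = [q1/(1 − q1)] / [q0/(1 − q0)].

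**Worked case** (p = 5%, s = 100%, r = 3% v 6%).
- Placebo: 0.05 + 0.95 × 0.03 = 0.0785.
- Simvastatin: 0.05 + 0.95 × 0.06 = 0.107.
- Risk ratio: 0.107/0.0785 = 1.36, against a true 2.00.
- Odds ratio: 1.41, against a true (0.06/0.94)/(0.03/0.97) = 2.06.
- Share of placebo events that are pre-existing: 0.05/0.0785 = 64%.
- Risk difference: 0.107 − 0.0785 = 2.85 points, against 3.0.

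**Observed odds ratio over the range** (s = 100% / s = 70%).

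| New-case risk | True OR | p = 2% | p = 5% | p = 10% |
|---|---|---|---|---|
| 3% v 6% | 2.06 | 1.65 / 1.73 | 1.41 / 1.49 | 1.25 / 1.32 |
| 5% v 10% | 2.11 | 1.81 / 1.88 | 1.57 / 1.66 | 1.38 / 1.47 |
| 3% v 9% | 3.20 | 2.33 / 2.51 | 1.84 / 2.02 | 1.52 / 1.66 |

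**What drives it.** If every prevalent case were below the threshold (s = 0), then at p = 10% the risks would be 0.027 v 0.054 and the odds ratio (0.054/0.946)/(0.027/0.973) = 2.06, almost unchanged. The attenuation comes from prevalent cases above the threshold.

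**Risk difference.** q1 − q0 = (1 − p)(r1 − r0), whatever s is. For 3% v 6% it goes from 3.0 to 2.94, 2.85 or 2.70 points at p = 2%, 5% or 10%.

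**Power** (two-sided 5%, worked case): about 14% with 75 non-diabetic participants per arm, and about 9% with all 79 per arm counted.

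**Events** (p = 5%, s = 70%, r = 3% v 6%): 79 × (0.0635 + 0.092) = 12.3 with everyone counted; 79 × 0.95 × (0.03 + 0.06) = 6.8 after restriction.

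**The case against.** The strongest reply is that the SAP never says existing diabetes counts as a new case. It uses the word incidence, which ordinarily means new onset, and it collects the status needed to apply that meaning. A careful analyst might restrict the risk set unprompted. That is a fair reading of intent, and a reader should not infer a deliberate choice to count prevalent cases. But the only rule written down is the HbA1c threshold, and an analyst who scored everyone with a 24-month result would be following the plan.

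The adjustments in 6.2 do not close the gap. Screening status is not a listed covariate. The extra adjustment for a visibly large baseline imbalance is a conditional sensitivity analysis and leaves the risk set unchanged.

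Three stronger claims are tempting and should not be made:
- *A statin effect is hidden to a known degree.* Every rate above is assumed. The exclusion of anyone needing a statin may keep prevalent cases few, and the risk difference barely moves.
- *The planned model cannot be fitted.* The SAP gives no event rate. Section 6.2 also plans models adjusted for baseline only, clarification (iii) removes the centre effect from them, and Table 9 has a diabetes row for them. With no baseline diabetes measure, this appears to reduce to a treatment-only model. Section 6.1 also promises frequencies and percentages.
- *Treated new cases could be recovered from concomitant medication.* The SAP describes recording PD medication and non-trial statins, but not glucose-lowering treatment.

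**Conclusion.** The point stands as a fault in how the outcome is specified. The written rule yields the 24-month prevalence of raised HbA1c under the name of incidence, in an outcome assigned to safety.

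On average the odds ratio moves towards 1, provided that prevalence and the share above the threshold are similar in the two arms. In a single trial, an uneven split of a few prevalent cases could shift it either way. For assumed new-case risks of 3% v 6%, a true odds ratio of 2.06 would appear as between 1.73 and 1.25 at 2% to 10% prevalence with 70% to 100% of prevalent cases above the threshold. The actual size cannot be known from the SAP.

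The consequence is limited. Section 8.2 treats secondary outcomes as exploratory, power is low under either definition, and the primary futility result does not depend on this outcome. The change is still worth making, because the needed variable is already held.

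**What to change.** - In 2.2.1 and 8.2, define the incidence analysis on participants recorded as having no diabetes at screening, scored by HbA1c of at least 6.5% at 24 months.
- Report the same threshold in all participants with a 24-month result, by arm, and label it prevalence. Match the labels in Tables 3 and 9.
- Optionally, also count new diabetes diagnoses recorded as adverse events, and say so in the definition.
- Give counts and percentages by arm beside any model estimate, and read the result descriptively.

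**Cost.** The core change is wording and uses data already collected. A few participants leave the denominator and the event count falls (from about 12 to 7 in the illustration above), so the model becomes sparser. The restriction is only as good as the screening record: the SAP shows no baseline HbA1c, so undiagnosed diabetes at entry would remain. The SAP's revision log records that allocations had been revealed by 24 August 2020, so a change to this version should be logged as made after unblinding, with both results shown.

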### **8.2.1 COVID-19 Sensitivity Analyses of Secondary Outcomes**

In line with the draft guidance on the implications of the COVID-19 outbreak on methodological aspects of ongoing clinical trials, additional sensitivity analyses of all secondary outcomes for which at least one participant provided valid 24-month data during COVID-19 lockdown will be undertaken. Specifically, the analyses of each of the secondary outcomes will be repeated excluding participants who provided 24-month outcome data during COVID-19 lockdown when social distancing measures were in place (i.e. the non-COVID-19 population). Comparison of the treatment effect estimates from these sensitivity analyses against the estimates obtained from the primary analyses of the secondary outcomes will facilitate informal evaluation of the effect of the pandemic on the secondary outcomes.

The number of capsules and percentage of capsules returned every month will also be presented according to whether 24-month outcome data was collected face-to-face or remotely.

## **9 SAFETY DATA**

---

Adverse event (AE) data gathered from telephone contacts and visits of participants included in the safety population will be used to determine the safety and tolerability of Simvastatin.

The number and percentage of adverse events (AEs) will be reported by participant's completion status (i.e. completed IMP, discontinued IMP and withdrew) and by treatment taken (i.e. placebo, 40mg only or 80mg). We will also report information on:

- Timing of withdrawal/discontinuation
- Severity of AEs prior to withdrawal/discontinuation
- Classification of AEs prior to withdrawal/discontinuation
- Whether the decision to withdraw/discontinue was blinded.

We will report summary statistics of AEs by treatment taken, and if the number of participants reporting at least one AE within an organ system classification exceeds 5% of the safety population, we will report the AE summary statistics by treatment taken for that particular organ system. The summary statistics of serious adverse events (SAEs) will be reported by treatment taken and organ system classification.

Any AEs and/or SAEs which are related to common known effects side of statins use, as listed in the BNF , will be reported by treatment taken. These include:

- Asthenia
- Constipation
- Diarrhoea
- Dizziness
- Flatulence
- Gastrointestinal discomfort
- Hepatitis
- Headache
- Myalgia
- Myopathy (including myositis)
- Nausea
- Sleep disorder
- Thrombocytopenia

The summary statistics of AEs and SAEs will include:

- Numbers and percentages of participants reporting at least one AE
- Numbers and percentages of participants reporting AEs by the total number of AEs participants have reported
- Numbers and percentages of participants reporting at least one SAE
- Numbers and percentages of participants reporting SAEs by the total number of SAEs participants have reported

In addition, we shall produce Kaplan-Meier curves of cumulative incidences of AEs and SAEs by treatment taken.

Although no formal hypothesis testing of the safety data will be conducted, 95% confidence intervals of proportions by treatment taken will be presented. Any notable increase in safety related events within the Simvastatin groups (40mg only or 80mg) compared to the control group will be investigated further.

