### 3.3 ANALYSIS POPULATIONS

We will base the primary analysis of the primary outcome on a modified intention-to-treat (mITT) principle. The mITT evaluable sample for the primary analysis will include all participants who are randomised, provide baseline outcome data, commence to the higher dose phase of the study and provide 24-month outcome data. Imputation will only be performed for missing questionnaire items that fulfil pre-specified criteria as outlined in section 4.10.

To investigate any effect of compliance with taking study medication, if  $\geq 20\%$  of participants in the active Simvastatin group are identified as non-compliers (according to each of the definitions in section 4.4.2), we will undertake additional sensitivity analyses of the primary outcome (further details in section 7.3.1). This population will consist of all participants with baseline and 24-month primary outcome data.

The safety population will consist of all participants who have at least one dose of allocated trial treatment.

A washout period has been included in the study design to explore the potential disease-modifying effect of Simvastatin. Trial treatment will be discontinued at 24 months and a follow-up visit is conducted two months later at 26 months post-baseline. All participants still on trial treatment at the higher dose of 80mg at 24 months with valid baseline, 24 and 26 months data will be included in the disease-modifying analysis.

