Hence  $\alpha$  and  $\beta$  were chosen to reflect the futility design-based hypotheses, with the one-sided  $\alpha$  set at 10% and  $\beta$  at 20% (i.e. 80% power).

Based on a recently reported study at the time of the design of this futility trial, the expected mean increase in MDS-UPDRS part III from baseline to 12 months in the placebo group is assumed to be 2.2 points, with corresponding standard deviation of 7.3 points. Assuming that this increase in MDS-UPDRS part III is linear over time, gives an expected mean increase from baseline to 24 months of 4.4 points in the placebo group (i.e.  $\mu_p = 4.4$ ). Therefore, if we assume the MCID is -3, this implies the mean of the Simvastatin group,  $\mu_s$ , is 1.4 points. Additionally, we assume a slightly inflated standard deviation over this period of 7.5 points.

The sample size calculation was based on a two-sample t-test with a 10% one-sided alpha. Following the previously listed assumptions, the number of participants needed to follow-up at 24 months (i.e. with primary outcome data) is 57 participants per group, to provide 80% power to reject the null hypothesis of non-futility and declare futility.

This sample size was inflated to allow for a proportion of participants allocated to the Simvastatin group to stop taking the trial medication during the initial 1-month low dose phase. Assuming that this proportion was 15%, the above sample size was inflated by  $(1-0.15)^{-2}$ , to give 79 participants per group. Secondly, the sample size was adjusted to allow for a (non-differential) loss to follow-up rate of 20%. Accordingly, the sample size was further inflated by a factor of  $(1-0.2)^{-1}$ , to give a sample size of 99 participants per group and a total recruitment target of 198 participants commencing the higher dose phase of the study.

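### Adverse events are compared by dose level reached and never by randomised arm, so the 80mg v placebo contrast is selected on tolerating the first month

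*SAP*

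**What the plan says.** Section 9 applies one grouping throughout. AE counts and percentages are given by completion status "and by treatment taken (i.e. placebo, 40mg only or 80mg". For the rest:

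- AE summaries: "We will report summary statistics of AEs by treatment taken", with organ-system detail where a 5% threshold is passed. The listed known statin effects follow the same grouping.
- SAE summaries: "will be reported by treatment taken and organ system classification".
- Intervals: "95% confidence intervals of proportions by treatment taken will be presented", with no formal testing.
- Curves: "we shall produce Kaplan-Meier curves of cumulative incidences of AEs and SAEs by treatment taken".
- Signal rule: "Any notable increase in safety related events within the Simvastatin groups (40mg only or 80mg) compared to the control group will be investigated further".

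Completion status is the only other stated cut of the AE data. No AE or SAE display is by allocated group or combines the two simvastatin columns, and treatment taken is not defined beyond its three labels.

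Three other places set the context. Section 3.3: "The safety population will consist of all participants who have at least one dose of allocated trial treatment". Section 3.1 gives all active participants 40mg for one month before 80mg. Section 4.2 allows for 15% of the simvastatin group to "stop taking the trial medication during the initial 1-month low dose phase".

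**The concern.** The dose level reached is settled after randomisation, and partly by how the participant tolerated the drug. The split is made in the active arm only. A simvastatin participant who stops in month 1 goes to the 40mg-only column. A placebo participant who stops in month 1 stays with all other placebo participants. The 80mg column has therefore been selected on getting through the first month, and its comparator has not.

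Safety and tolerability is secondary objective (i) in section 2.2, and section 7.2.1 says that the safety results should inform the final decision on futility. The primary analysis already leaves out anyone who never starts the higher dose (section 3.3), so section 9 is where early intolerance ought to be seen against a fair control. The revision of 27 July 2020 records that the data needed to attribute a discontinuation to an adverse event were not obtained, so a table of discontinuations due to adverse events cannot fill the gap. Cholesterol and incident diabetes, which section 8.1 lists as safety outcomes, are compared by allocated group under section 8.2. Adverse events are not.

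**Working it through.** **Inputs from the SAP.** Stopping share in the low-dose month s = 15%; 99 per group (both section 4.2). The sample-size chain behind these reproduces. A two-sample test with a 3-point difference, SD 7.5, one-sided 10% alpha and 80% power needs 57 per group. 57/(0.85)² = 78.9, so 79. 79/0.80 = 98.75, so 99. This chain is not in dispute; it supplies the 15%.

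**Assumed inputs.** The SAP gives no AE rates. Let p0 be the placebo risk, p80 the risk in those who reach 80mg and f the risk in those who stop before 80mg.

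**Formula.** Whole-arm simvastatin risk = s·f + (1 − s)·p80.

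**Case 1: early harm only.** Set p80 = p0. The 80mg v placebo difference is then zero by construction, and the arm-level excess is s·(f − p0).

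| s | p0 | f = 50% | f = 100% | 80mg v placebo |
|---|---|---|---|---|
| 15% | 10% | 0.15 × 0.40 = +6.0 points | 0.15 × 0.90 = +13.5 points | 0 |
| 15% | 20% | 0.15 × 0.30 = +4.5 points | 0.15 × 0.80 = +12.0 points | 0 |
| 15% | 40% | 0.15 × 0.10 = +1.5 points | 0.15 × 0.60 = +9.0 points | 0 |
| 5% | 10% | 0.05 × 0.40 = +2.0 points | 0.05 × 0.90 = +4.5 points | 0 |

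The amount concealed shrinks as the background risk rises or fewer people stop early.

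**Case 2: no drug effect at all.** Set the whole-arm risk equal to p0 = 40% with s = 15%. Then p80 = (p0 − s·f)/(1 − s).

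- f = 70%: (0.40 − 0.105)/0.85 = 34.7%, an apparent benefit of 5.3 points.
- f = 100%: (0.40 − 0.15)/0.85 = 29.4%, an apparent benefit of 10.6 points.

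In the same case the 40mg-only column reads 70% to 100% against 40% for placebo, an apparent harm that is equally spurious.

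**Precision.** On a base of 99, the 40mg-only column holds 0.15 × 99 ≈ 15 people. With 7/15 events its Wilson 95% interval is 25% to 70%.

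**Base.** Section 3.1 randomises 198 in total, whereas section 4.2 has 198 commencing the higher dose, which would mean 99/0.85 ≈ 116 randomised per arm. The counts change with the reading. The percentages above depend only on s, f and p0, and do not.

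**The case against.** **Harm is not hidden.** A reader might infer that the plan conceals early harm. It does not. The 40mg-only group has its own column and interval, and the signal rule names it. The split can even make early harm more conspicuous. Suppose background risk is 20% and 10 of 15 stoppers have a drug-caused event. Then 40mg only shows 10 + 0.2 × 5 = 11/15 (Wilson 48% to 89%) against placebo 20/99 (about 13% to 29%), Fisher p < 0.001. Pooled, it is (17 + 11)/99 = 28/99 against 20/99, p = 0.25. This stands as far as visibility goes. It does not make the contrast fair: case 2 shows the same alarm arising with no drug effect, because early stoppers are set against all placebo participants. Participant counts in the two simvastatin columns can be added back to recover the arm. The intervals and curves cannot.

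**There is no immortal time.** It is tempting to say that the 80mg curve contains a guaranteed event-free month. It does not: a participant with an event in month 1 who then escalates keeps that event in the 80mg curve. The fault is selection on tolerance, which is weaker. It also concerns only those who never reach 80mg; later dose reducers (section 4.4.2) appear to remain in the 80mg column.

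**Other displays help.** Section 9 also cuts AEs by completion status, and reports the timing of discontinuation and the severity and class of prior events. Section 5 reports how many progress to the higher dose, with reasons for those who do not. Section 5.2 summarises low-dose-only participants, and section 8.2 reports capsules by allocated group. If completion status were crossed with treatment taken, placebo discontinuers would be visible too; the text permits this but does not state it. These displays inform tolerability. None is an adverse-event comparison of the randomised arms.

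**Conclusion.** The point holds: section 9 plans no randomised comparison of adverse events, and the 80mg v placebo contrast that it offers tends to understate early harm or to suggest benefit where there is none. At the plan's 15% stopping rate, an arm-level excess of 4.5 to 12.0 points (placebo risk 20%) or 6.0 to 13.5 points (placebo risk 10%) would show as zero. These figures assume that those reaching 80mg carry placebo risk and that 50% to 100% of stoppers have an event. They illustrate the mechanism and do not estimate this trial's event rates.

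This should be fixed. A reader might think it serious enough to undermine the trial's main conclusion, but the futility test is untouched, safety is not formally tested, and the early events remain on view in the 40mg-only group.

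**What to change.** In section 9:

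1. Make simvastatin (any dose) v placebo, by randomised arm in the safety population, the main display for every AE and SAE table, 95% interval and Kaplan-Meier curve.
2. Apply the rule on notable increases to that comparison as well as to the dose groups.
3. Keep the dose-level split as a descriptive supplement, so that the early signal in the 40mg-only group is still seen.
4. Define treatment taken, stating where people who stay on 40mg, and those who reduce to 40mg after reaching 80mg, are counted.
5. Label any dose-specific curve as a non-randomised comparison. Starting the 80mg curve at escalation, against placebo participants who passed the same visit, would not remove the need for this label, because both groups would still be conditioned on a post-randomisation event.

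The cost is some SAP wording, one extra column per table and one extra set of curves, all from data already collected. The SAP was last revised after allocations were revealed (24 August 2020), so the change should be dated and marked as made after that point.
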